### Outcome variables

The primary outcome of this study is the completion of CCS within 6 months in both the intervention group and control group (9–36, 39–41). Above 50% will indicate optimal screening uptake. The secondary outcome is the change in the level of knowledge, awareness, intention, and health beliefs toward cervical cancer and screening among the patient navigators and COMW after the training and education sessions (9, 47–50). For group items, >50% will indicate adequate knowledge, positive attitude, positive health beliefs, and being unaware of cervical cancer and CCS. Social demographic characteristics will be assessed to identify their association with the uptake of CCS services.

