## Abstract

**Aim:**

There are limited studies in Tanzania concerning the modality of preparing patient navigators and the influence of patient navigation strategies on cervical cancer screening. This protocol describes the preparation of patient navigators and assesses the impact of a patient navigation strategy on promoting cervical cancer screening uptake, knowledge, awareness, intention, and health beliefs.

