#### Sample size determination of COMW

The sample size for the COMW has been calculated through G-Power software (42) and is based on the outcome variable of completion of screening at a 6-month follow-up. Using the F-test, with an effect size of f = 0.3, α err prob = 0.05, and power (1 − β err prob) = 0.83, the sample size of community women to be recruited will be 202 (intervention group = 101 and control group = 101).

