### Analysis

All data will be entered and analyzed in SPSS version 21 software. To analyze the data from CHWs before and after their training, frequency and proportion will be used for the categorical variables and means for the continuous variables. Changes in knowledge, attitude, health beliefs, and screening intention will be analyzed using the independent sample *t*-test and linear regression.

The data from the COMW at baseline, 3-month follow-up, and 6-month follow-up will be analyzed using descriptive statistics (frequency and proportion), the independent sample *t*-test, linear regression, and a repeated measures ANOVA. Furthermore, principal components analysis (PCA) will be used to identify the frequency (*N*) and percentage (%) of respondents with awareness, knowledge, subjective norms, perceived behavioral control, and health beliefs regarding cervical cancer and CCS.

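### The cut-off for awareness points the wrong way as written, and principal components analysis is given a counting task that it does not perform on its own

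*Protocol article*

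**What the plan says.** Two sections of the protocol article bear on this point.

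- **Outcome variables.** Awareness is among the secondary outcomes: "The secondary outcome is the change in the level of knowledge, awareness, intention, and health beliefs toward cervical cancer and screening". The rule that turns these measures into categories follows: "For group items, >50% will indicate adequate knowledge, positive attitude, positive health beliefs, and being unaware of cervical cancer and CCS".
- **Analysis.** After the planned tests for the community women, the article adds that "principal components analysis (PCA) will be used to identify the frequency (*N*) and percentage (%) of respondents with awareness, knowledge, subjective norms", and continues with the remaining constructs. The sentence just before it already names a method for counts: the data "will be analyzed using descriptive statistics (frequency and proportion), the independent sample *t*-test, linear regression, and a repeated measures ANOVA".

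The intended direction is clear from the Aim in the Abstract, which says that the protocol "assesses the impact of a patient navigation strategy on promoting cervical cancer screening uptake, knowledge, awareness, intention, and health beliefs". Table 3, under Data collection and measures, describes awareness as one dimension with two Yes/No items and knowledge as 24 items on a 3-point scale. It mentions no reverse scoring.

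**The concern.** There are two separate faults.

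**Direction of awareness.** Adequate knowledge, a positive attitude and positive beliefs are what the intervention should produce; being unaware is what it should reduce. All four are attached to exceeding the same threshold. An analyst who programs the rule as written, with Yes scored as aware, would put the most aware women in the unaware category, and a gain in awareness would be tabulated as a loss.

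**Source of the counts.** PCA summarises the correlation among items as weighted components. It does not say how many respondents possess a construct. To get a count, someone must choose a score and a cut. The article states one cut, the 50% rule, in a different section and does not connect it to PCA. Two routes to the same frequencies are therefore on the page (PCA, and descriptive statistics), with nothing to say which governs, and they need not agree.

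**Working it through.** The article gives no figure to reproduce here, so the check is on the text, plus one enumeration and one illustration.

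**1. Labels side by side (Outcome variables).** Above 50% means:

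| Construct | Label above 50% | Direction |
|---|---|---|
| Knowledge | adequate | favourable |
| Attitude | positive | favourable |
| Health beliefs | positive | favourable |
| Awareness | unaware | unfavourable |

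The last row conflicts with the Aim unless a higher awareness value means less awareness, and no such coding is stated.

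**2. Possible awareness scores (Table 3: two Yes/No items).** Reading the 50% as a share of the maximum score, with one point per Yes:

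- 0/2 = 0%
- 1/2 = 50%
- 2/2 = 100%

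Only 2/2 exceeds 50%. If Yes means aware, the women labelled unaware are exactly those who answered Yes to both items. This step depends on that reading and that coding, neither of which the article gives.

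**3. Does PCA yield a count?** A component score is a weighted sum of centred items, so its sample mean is 0 by construction, and its sign is arbitrary. It becomes a count only after a cut is chosen, and the Analysis section gives none.

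**4. Can a PCA split disagree with the 50% rule?** Assumptions, none of them from the article: 202 women (the planned total) in each of three scenarios; 24 items scored 0 to 2 (maximum 48); one underlying trait with standard deviation 1 and mean −1.5, 0 or 1.5; PCA fitted afresh in each scenario to standardised items; cut at a first-component score of 0. One simulated sample per scenario.

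| Knowledge level | Raw score above 50% | First component above 0 | Same, sign reversed |
|---|---|---|---|
| Low | 5/202 = 2.5% | 73/202 = 36.1% | 129/202 = 63.9% |
| Middle | 95/202 = 47.0% | 97/202 = 48.0% | 105/202 = 52.0% |
| High | 185/202 = 91.6% | 128/202 = 63.4% | 74/202 = 36.6% |

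From low to high knowledge the raw-score rule moves by 91.6 − 2.5 = 89.1 percentage points. The component split moves by 63.4 − 36.1 = 27.3 points. The two agree closely only in the middle scenario. A split of this kind follows the sample's own mean rather than an absolute level of knowledge.

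**The case against.** The case on the other side has several parts.

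- **The label is probably a one-word slip.** Every other term in the list is favourable and the Aim is plain, so an analyst would probably correct it. That makes misreporting less likely, but the word stands in the sentence that defines the category and still has to be corrected.
- **The threshold may not be a score.** The article speaks of group items, and shortly before applies an above-50% criterion to screening uptake, which is a proportion of women. If respondents are meant here too, the enumeration of 0, 50 and 100% does not apply. This stands as a limit on step 2. It does not rescue the label, which points the wrong way on any reading unless the items are reverse-coded, and it shows that the denominator needs stating.
- **PCA can be a first step to an index that is then cut.** True, and the cut could sit in a fuller document. But what is written gives the counting to PCA itself, beside a 50% rule that is never tied to it.

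Three stronger readings are tempting, and the document does not support them.

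- A reader might infer that PCA would label about half the women adequate at every visit. That needs a cut at zero, refitting at each visit and symmetric scores; even with the first two, the simulation gave 36% to 63%.
- A reader might infer that the arms could not be compared. If PCA is fitted to both arms together, all women share one component, centre and sign, and the arms are comparable at that visit. With loadings and centring fixed from one visit, comparison over time is possible too.
- A reader might infer that cutting at 50% discards the information on change. The Analysis section already plans t-tests, linear regression and repeated measures ANOVA, which imply continuous scores, and nothing says that the categories replace them.

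**Conclusion.** Wrong as written, on two counts. The awareness category is reversed unless an unstated reverse coding applies. PCA is named as the source of frequencies that it does not supply alone, with no stated cut and no link to the article's 50% rule.

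The direction fault rests on the text alone. That it would affect exactly the women answering Yes to both items is conditional on a score-based reading and on Yes meaning aware. The simulated percentages show only that the two routes can diverge widely; they do not predict this trial's results. Nor does the text establish that a benefit will in fact be published as harm: that would happen only if the sentence were followed literally.

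The reach is confined to secondary, descriptive classifications. Screening completion within 6 months, the primary outcome, and the planned 202 women are unaffected.

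**What to change.** **Outcome variables.** Make above 50% indicate being aware, or keep the present label and state that the two items are reverse-coded. Say what the 50% is a percentage of: maximum score, items or respondents. If it is the maximum score with one point per Yes, note that a woman with one Yes scores exactly 50% and does not exceed the cut.

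**Analysis.** Remove PCA as the source of the number and percentage of respondents. Compute these with the descriptive statistics already planned, from the scale scores, using the same fixed 50% cut at every visit and in both arms. If PCA is kept, limit it to examining the dimensions of the questionnaires.

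The cost is a few sentences of text. No new data are needed, and neither the sample size nor the primary analysis changes.

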### Ethical consideration

The study protocol was approved by the University of Dodoma Research Ethical Committee with approval number (UDOM/DRP/134/VOL IV/42). An informed consent form will be signed by each participant to indicate their willingness to participate. The participants will have the freedom to withdraw from the study if they wish to do so. The records of this study will be kept private.

## Discussion

More funds have been spent to train health professionals and send them to communities to promote awareness of the disease and speak on the significance of screening tests (51). Despite these efforts, the proportion of women utilizing screening services remains small (16, 50–53). Several factors have been reported that hinder women from attending screening services in Tanzania in different studies, including a lack of support from their husbands, long distance to the screening clinics, and cultural norms (11), but a knowledge deficit about cervical cancer is considered the main hindrance and this should be addressed to increase the participation of women in CCS services (52).

The training of patient navigators in Tanzania is possible as women with a secondary education level and above are available and most of them are not employed. Furthermore, the training of patient navigators is possible because Tanzania currently has nurses and doctors in oncology who are capable of conducting the training of patient navigators.

The outcome of patient navigation is hypothetically assumed to be positive, with increases in screening uptake and knowledge, positive health beliefs, and intention. This should be associated with the proximity of the patient navigators and the COMW. Since they live in the same area, know each other, and share most of the cultural elements, they are likely to listen to each other and cooperate on whatever is agreed. When patient navigators deliver health education, it is likely to be well received and understood because it is delivered in a non-formal structure. Furthermore, when the patient navigators ask the COMW to screen for cervical cancer, they are likely to do so because the patient navigators could conduct a follow-up at any time at their homes. Therefore, COMW may screen not because of health education, but because they know the patient navigators will conduct a follow-up. Meanwhile, when women are asked to become patient navigators, they accept because they know it will benefit them financially. Since they consider this work as employment, an allowance inevitably amplifies their commitment to learning and implementing. Therefore, based on the definition that patient navigators can be volunteer or be paid, in the Tanzanian context, paying patient navigators is good, as volunteering could be associated with the poor implementation of patient navigation. This is consistent with a previous study that reported that patient navigators’ incentives and remuneration are core issues that affect the performance of individual patient navigators and the overall performance of the CHW program. This previous study recommends that patient navigators receive a financial package that corresponds to their job demands, complexity, number of hours worked, training, and the roles they undertake (54).

The patient navigators will deliver education to community women aged ≥21 and ≤75 years old (18–23, 25, 27–29). They must be willing to participate in the study (21–23), have no previous history of cancer or medical problem (20, 23, 25, 27, 28), speak their native language or English (19, 21, 23), have no plan to change their living residence during the study period (19, 23, 27), be non-adherent to the screening test guidelines (20, 25, 28), and have not undergone previous screening tests (21, 22). A one-time education session conducted by trained lay personnel lasting for 2 h is recommended to be adequate for imparting knowledge to women (21, 28). The education should be conducted in small groups of four to eight community women (19–23, 28). Community women should complete the screening test within 6 months after receiving the education from the trained lay personnel (18, 19, 21, 23, 29). The educational sessions conducted by trained lay personnel should be paired with other educational materials (18–23, 25, 29). After the educational intervention, the patient navigators will provide navigation services to women including financial assistance, organizing transportation services and childcare, and assisting women with language barriers to attend the screening tests (19–21, 24, 25). The patient navigators will also schedule appointment dates for the women (24, 25). The patient navigators will conduct a follow-up by telephone, a letter, mail, or home visits (19–24, 28) to remind the women to go for screening or identify their barriers to doing so. The follow-up is commonly conducted 6 months after the education is delivered to the community women (20, 21, 28).
